### Adverse events

2.12

In research, some adverse reactions may occur.

1.There are a few common responses after the acupoint catgut embedding:Local reactions: Mostly some sterile inflammations with inflamed hot pain occur within 5 days. Some cases may be more severe, like a small amount of milky-white exudation at the embedding spot caused by fat liquefaction because of suture stimulation. Circumstances above should not require any special treatment.General reactions: Some patients may experience temperature rising after treatment 4 to 24 hours, mostly around 38. It will fade away in 2 to 4 days by itself. Usually, hemogram of each patient may rise in different levels, and it will return to normal in 3 to 5 days.2.There are a few adverse responses after the acupoint catgut embedding:Pain: Apply hot compress if there is pain at embedding acupoint.Secondary infections: Lack of strict asepsis and inappropriate protection for the wound could cause secondary infection, which mostly brings about some inflammatory symptoms like local swelling, progressive pain, and fever in 3 to 4 days after the implantation. Hot compress and anti-infective treatment would be helpful.Nerve injuries: It is usually caused by an incorrect operation or excessive stimulation or carelessness, and can be avoided with careful operation.Hemorrhage: It is usually caused by a puncture on the vessels or excessive stimulation. Pressure put on the puncture point would stop the bleeding.Suture allergies: Local itching or swelling or fever can be remitted by antianaphylaxis treatment.3.Alprazolam is one of the Benzodiazepines. Its principal effects are anti-anxiety and antidepressant. Common adverse reactions are as following:Somnolence, vertigo, and weakness, etc. The large dose may cause dystaxia, tremor, uroschesis or jaundice.Addiction. Drug withdrawal may cause withdrawal symptoms after being used for a long period, showing as emotional or melancholy.A few patients may suffer dry mouth, inattention, hyperhidrosis, palpitation, constipation or diarrhea, blurred vision, and hypotension.

### Sample size calculations

2.13

Based on preliminary experiments, it is obtained that after treatment the Kuppermann index (MI) of the intervention group dropped 15.90 ± 2.71, while the control group dropped 13.84 ± 1.87, the population standard deviation S = 2.12, δ = 2.06. Given α = 0.05 bilateral, β = 0.1, power of test 1−β = 0.9, based on formula^[15]^: n = 2 × [(tα+t2β) × s/δ] × [(tα+t2β) × s/δ], calculating with trial and error method, we used table look-up: tα, ∞ = 1.96, t2β, ∞ = 1.282, then we obtained n = 23.66 ≈ 24. According to t table: t0.05(24 × 2−2) = 2.0129, t0.2(24 × 2−2) = 1.3002, we substituted it into the former formula and obtain n = 23.25 ≈ 24, the sample size was plateaued, and the attempts stopped, which means each group requires 24 samples, and 2 groups require 48 samples in total (n = 48). With the consideration of the maximum loss rate of follow up is 20%, we concluded that the total sample size is 60. According to HAMA Score (14 items contained), the sample size is 14 × 5 = 70. Take two parts above into consideration, the sample size is determined at 70.

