#### Primary endpoint

2.10.1

The primary outcomes of this study will be changes in the frequency of panic attack and in the PDSS and PASS during the observation period (3 months) and follow-up period (1 month), analyzed in both groups. After baseline time, they will be tested at week 0, week 4, week 8 and week 12, and during the follow-up period.

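### The 90% power in section 2.13 is calculated on the Kupperman index, and N = 70 comes from a HAMA item count, so the stated power applies to none of the primary outcomes

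*Protocol article*

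**What the plan says.** Section 2.13 (Sample size calculations) starts from preliminary experiments: "it is obtained that after treatment the Kuppermann index (MI) of the intervention group dropped 15.90 ± 2.71". The corresponding fall in the other arm is given as 13.84 with an SD of 1.87. From these it takes "the population standard deviation S = 2.12, δ = 2.06", a two-sided alpha of 0.05 and power of 0.9. It concludes that "each group requires 24 samples, and 2 groups require 48 samples in total". Allowing for dropout, it states that "the maximum loss rate of follow up is 20%, we concluded that the total sample size is 60".

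A second rule follows: "According to HAMA Score (14 items contained), the sample size is 14 × 5 = 70". Both results are considered and N is set at 70, that is, 35 per arm (section 2.1).

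Section 2.10.1 (Primary endpoint) names different variables: "The primary outcomes of this study will be changes in the frequency of panic attack and in the PDSS and PASS". These are followed through the 3-month observation period and the 1-month follow-up. HAMA and SCL-90 are secondary (section 2.10.2). The baseline and 4-weekly assessments in section 2.9 are attack frequency, PDSS, PASS, HAMA and SCL-90. The Kupperman index is not mentioned outside section 2.13.

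**The concern.** Power belongs to one comparison of one variable, with its own expected difference and SD. Here the difference, the SD and the 90% all belong to the Kupperman index, which measures menopausal symptoms. The protocol does not present it as a stand-in for panic outcomes and gives no correlation with them.

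The step that fixes the final N contains no effect size, variance, alpha or power. A patients-per-item ratio cannot size a comparison of two means, and HAMA is not a primary outcome.

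What is at stake is how a non-significant primary result will be read. Section 2.14 decides by a 0.05 threshold, and the comparator is an active drug, alprazolam. A reader who takes the trial to have 90% power could treat a null result on PDSS, PASS or attack frequency as evidence that the treatments do not differ. Nothing in the document supports that reading.

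**Working it through.** **1. Reproducing the plan's figures** (all inputs from section 2.13)

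- δ = 15.90 − 13.84 = 2.06; S = 2.12; δ/S = 0.97.
- The plan's formula is n per arm = 2[(t_α + t_2β)S/δ]².
- With the plan's t values for 46 degrees of freedom: 2 × [(2.0129 + 1.3002) × 2.12/2.06]² = 23.25, so 24 per arm, as stated.
- By the noncentral t distribution, 24 per arm gives power 0.909, and 24 is the smallest n that reaches 0.90.
- Dropout: 48/(1 − 0.20) = 60. Item rule: 14 × 5 = 70.

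The figures 24, 48, 60 and 70 all reproduce. The fault lies in what they are calculated on.

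Two side points do not change the conclusion. With S = 2.12 the first pass gives 2 × [(1.96 + 1.282) × 2.12/2.06]² = 22.26, not the printed 23.66. Also, the pooled SD of 2.71 and 1.87 with equal arms is √[(2.71² + 1.87²)/2] = 2.33, not 2.12. The pilot arm sizes are not given, so unequal arms could explain 2.12.

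**2. Setting the sections side by side**

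| Variable | Role in the text | Used in section 2.13 |
|---|---|---|
| Kupperman index | none listed | δ, S, 90% power |
| HAMA | secondary | item count sets N = 70 |
| Attack frequency, PDSS, PASS | primary | not used |

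**3. What N = 70 can detect**

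The document gives no difference or SD for any primary, so a required N cannot be calculated for them. What can be calculated is the detectable standardised difference d at the planned size. Inputs are 35 per arm and 35 × 0.80 = 28 after the plan's 20% loss. For two equal arms of n, the noncentrality is d√(n/2) with 2n − 2 degrees of freedom, and d is solved for the required power. This assumes a continuous outcome, one time point and a two-sided t test.

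| n per arm | Alpha | d at 80% power | d at 90% power |
|---|---|---|---|
| 28 | 0.05 | 0.76 | 0.88 |
| 35 | 0.05 | 0.68 | 0.79 |
| 28 | 0.05/3 = 0.0167 | 0.89 | 1.01 |

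The last row is an assumption: an equal split of alpha over the three primaries. The protocol does not state one.

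**4. Power at assumed effects** (two-sided 0.05, one test)

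| Assumed d | 28 per arm | 35 per arm |
|---|---|---|
| 0.5 | 45% | 54% |
| 0.3 | 20% | 24% |

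The values 0.5 and 0.3 are chosen for illustration and do not come from the document.

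**The case against.** The trial calls itself exploratory, and an exploratory trial may go without a formal power claim. Section 2.13 also ties its 90% to the Kupperman index by name and does not claim it for the primaries. This lowers the stakes but does not remove the point. The protocol does give an explicit power figure as the basis for its size, and the Discussion says the study aims to prove clinical effect.

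The item rule does no harm to power: 70 is the larger of 60 and 70, so it adds 10 patients. That stands. The objection to it is that it justifies nothing, not that it makes the trial smaller.

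A reader might go further in two ways, and the documents support neither.

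- **That the index is never measured.** Table 1, the schedule of assessments, is not shown, so the text supports only that the index is not among the listed outcomes and assessments. Even if it were scheduled, it would not be a primary outcome.
- **That the trial is shown to be too small.** With no difference or SD for any primary, a shortage of patients cannot be demonstrated. On the index itself N = 70 is ample: 28 per arm gives about 95% power at 0.97 SD. With the pooled SD of 2.33 the effect is 2.06/2.33 = 0.88 SD, and power is still 90%.

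**Conclusion.** The concern holds as a mismatch between the power calculation and the endpoints. The stated 90% power applies to none of the three primary outcomes, and the final N rests on a count unrelated to the planned comparison. An analysis plan written later could not cure this, because the protocol sets out its derivation in full on another variable.

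After the plan's own losses, the sensitivity for PDSS or PASS change is 0.76 SD at 80% power and 0.88 SD at 90%, for one test at one time point. An equal three-way alpha split raises these to about 0.89 and 1.01 SD. These figures do not carry over directly to attack frequency, which is a count, or to the rank-sum test that section 2.14 uses for non-normal data.

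The 45% and 20% power at 0.5 and 0.3 SD are illustrations under assumed effects. They are not estimates of this trial's power.

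**What to change.** Keep N = 70. In section 2.13, stop presenting the Kupperman calculation and the 14 × 5 rule as the basis of the trial's power. State the sensitivity for the primary outcomes instead, for example:

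*With 35 patients per arm, 28 after 20% loss, the trial has 80%/90% power to detect a standardised difference of 0.76/0.88 in [named continuous primary outcome] at [named time point], two-sided alpha 0.05. Smaller differences will be estimated with 95% confidence intervals and are not ruled out.*

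The sponsor should name the outcome and time point, since section 2.10.1 lists three primaries measured repeatedly. If all three remain co-equal with alpha split equally, the figures become about 0.89/1.01. If a pilot SD for PDSS or PASS exists, convert the difference to scale points. Attack frequency needs its own statement, suited to a count.

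A detectable difference worked back from a fixed N describes sensitivity but does not justify the size. The text should therefore say plainly how 70 was reached, without claiming that power for the primaries determined it.

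The cost is a rewording of one section, with no extra patients. The downside is that the stated power becomes less favourable.

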### Statistical analysis

2.14

Image data processing: using methods like independent component analysis (ICA) and function binding, applying professional software such as MRIcro for windows, Xjview 8.1, SPM 12 and MATLAB 5.1.

Statistical analysis technique: to apply a statistical test to the difference of prior-treatment and post-treatment, and to examine the curative effect difference within groups and among groups of all curative effect indexes. We will adopt the two-sided test for all statistical tests. It's considered that the tested differences are statistically significant if *P* less than or equal to 0.05. If *P* greater than or equal to .05, the tested differences are not statistically significant. Details are as following.

Measurement data: The *t* test will be adapted to run comparison among groups. When it doesn’t comply with the normal distribution, we will choose Wilcoxon rank-sum test. Similarly, we will run paired *t* test towards the difference of prior-treatment and post-treatment, and it will be changed into Wilcoxon rank-sum test while it does not comply with the normal distribution.

Enumeration data: We will use the Chi-square test, calibration Chi-square test, and Fisher exact method to run comparison among groups.

Ranked data: Wilcoxon rank-sum test will be applied to run comparison among groups and signed rank-sum test to run comparison within groups.

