### Intervention

2.9

At the screening visit, participants will sign the informed consent form. In a baseline questionnaire, information will be obtained age, occupation (physical/non-physical), education level, last menstrual period, previous use of acupuncture and expectation to acupoint catgut embedding therapy. Moreover, Panic Disorder Severity Score (PDSS), Panic-associated Symptoms Score (PASS), Hamilton Anxiety Scale (HAMA), Symptom Checklist 90 (SCL-90) must be completed at the baseline (week 0). The frequency of panic attack will also be recorded. Thereafter, study subjects will be randomized. There is a 3-months study period and a 1-month follow-up period for each group. In the study period, the frequency of panic attack, PDSS, PASS, HAMA Score and SCL-90 Score will be evaluated every 4 weeks. fMRI and 1H-MRS will be tested two times: in week 0 and week 12. A detailed process flow according to the SPIRIT figure can be seen in Table 1.

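### Arms are compared by an unadjusted t or rank-sum test although every clinical outcome is measured before randomisation; the test is valid, but it loses precision and leaves chance baseline imbalance in the estimate

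*Protocol article*

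**What the plan says.** Section 2.14 (Statistical analysis) fixes the between-arm method for measurement data: "The *t* test will be adapted to run comparison among groups". The fallback is "When it doesn’t comply with the normal distribution, we will choose Wilcoxon rank-sum test". No covariate and no regression model appears anywhere in the article.

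The article does not say outright whether the between-arm test uses follow-up values or changes, but the wording favours changes. Section 2.10.1 says "The primary outcomes of this study will be changes in the frequency of panic attack and in the PDSS and PASS", section 2.14 speaks of a plan "to apply a statistical test to the difference of prior-treatment and post-treatment", and section 2.13 sizes the trial on drops from baseline.

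Baseline data are complete by design. Section 2.9 says that PDSS, PASS, HAMA and SCL-90 "must be completed at the baseline (week 0"), and adds: "The frequency of panic attack will also be recorded". Randomisation follows these measurements. Sections 2.10.1 and 2.10.2 place the outcome assessments at weeks 0, 4, 8 and 12 and in the follow-up period.

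**The concern.** A two-sample test uses baseline badly in either form. On follow-up scores it ignores baseline. On change scores it subtracts the whole baseline value, which over-corrects whenever the regression slope of follow-up on baseline is below 1. Both forms leave residual variance that a measured covariate could remove, and both carry part of any chance baseline difference into the estimate, with opposite signs.

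With 70 patients, and fewer after dropout, this affects the width of the confidence interval and how easily a result can be read when the arms happen to differ at entry. Attack frequency, one of the three primary outcomes, is a count. A t or rank-sum test on it is usable but does not give a rate ratio.

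**Working it through.** **Inputs from the protocol article.** 35 per arm (2.1); maximum loss 20% (2.13), so 35 × 0.8 = 28 per arm; two-sided alpha 0.05; S = 2.12 and δ = 2.06 for the drop in the Kuppermann index (2.13).

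**Assumed, because the documents do not give it.** Correlation ρ between baseline and follow-up score of 0.3, 0.5 or 0.7; equal variance at baseline and follow-up; a common linear slope.

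**The plan's own figure.** n = 2 × [(2.0129 + 1.3002) × 2.12/2.06]² = 23.25, so 24 per arm, 48 in total, and 48/0.8 = 60 with loss, as stated. The first step with 1.96 and 1.282 gives 22.26, not the printed 23.66; the final 24 is unaffected.

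**Variance of the between-arm difference**, with the follow-up-score t test set to 1: change score 2(1 − ρ); ANCOVA 1 − ρ². Hence ANCOVA/change = (1 − ρ²)/[2(1 − ρ)] = (1 + ρ)/2.

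| ρ | change score | ANCOVA | ANCOVA/change | ANCOVA/follow-up |
|---|---|---|---|---|
| 0.3 | 1.40 | 0.91 | 0.65 | 0.91 |
| 0.5 | 1.00 | 0.75 | 0.75 | 0.75 |
| 0.7 | 0.60 | 0.51 | 0.85 | 0.51 |

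Read as equivalent size, 70 patients analysed by ANCOVA act like about 108, 93 or 82 analysed by a change-score t test, and like about 77, 93 or 137 analysed by a follow-up-score t test.

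**Detectable difference.** At 28 per arm and 80% power, the follow-up-score t test detects 0.76 SD. At ρ = 0.5, where the two unadjusted tests have equal variance, ANCOVA detects 0.76 × √0.75 = 0.66 SD; 28/0.75 = 37.3, so 28 per arm acts like about 37.

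**Power at 35 per arm for an assumed true difference of 0.5 SD** (noncentral t), at ρ = 0.3, 0.5, 0.7:
- follow-up score: 54% throughout
- change score: 41%, 54%, 76%
- ANCOVA: 58%, 66%, 82%

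**Chance imbalance at 35 per arm.** The baseline mean difference has standard deviation √(2/35) = 0.24 SD, so its 95% range is ±1.96 × 0.24 = ±0.47 SD. The chance of a gap above 0.3 SD is 2[1 − Φ(0.3/0.239)] = 0.21. A 0.3 SD gap shifts the follow-up-score estimate by 0.3ρ = 0.09, 0.15, 0.21 SD, and the change-score estimate by −0.3(1 − ρ) = −0.21, −0.15, −0.09 SD. ANCOVA removes this linear part.

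**On the plan's own inputs**, reading S as the SD of the drop, the residual SD under ANCOVA is 2.12 × √[(1 + ρ)/2]. By the normal formula, the number per arm for 90% power falls from 23 to 15, 17 or 19.

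**The case against.** The strongest reply is that a two-sample test is a conventional and valid analysis of a randomised trial. Its standard error already allows for chance imbalance, the trial is labelled exploratory, and an unseen analysis plan might add covariates. The validity part stands in full. The appeal to an unseen plan does not: the article names the test itself, and a plan that followed it would inherit the choice.

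A second reply is that change scores already use baseline, so the most striking ratio (0.51, against follow-up scores) belongs to the less likely reading. That is fair. The gain still survives: (1 + ρ)/2 is below 1 for any ρ below 1, although at ρ = 0.7 it is only 15%. Against follow-up scores the gain is only 9% at ρ = 0.3, and the HAMA entry threshold of 14 may lower ρ for that scale.

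A reader might infer three stronger claims that the documents do not support.
- That the planned test is biased or inflates type I error. It does neither; the bias is conditional on the imbalance actually observed.
- That imbalance is likely because randomisation is simple. Section 2.7 never calls it simple and fixes 35 per group, and a gap above 0.3 SD occurs in about one trial in five per outcome.
- That 90% power cannot be reached without adjustment. On the Kuppermann inputs the t test has about 98% power at 35 per arm and 95% at 28. But that index is not a listed outcome, so the figure says nothing either way about PDSS, PASS or attack frequency.

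**Conclusion.** The point holds as a matter of efficiency and of conditional bias, not as an error of validity. The plan should adjust for baseline. On the likelier change-score reading, ANCOVA cuts the variance by 35%, 25% or 15% at ρ = 0.3, 0.5 or 0.7; on the follow-up-score reading it cuts it by 9%, 25% or 49%. These sizes rest on an assumed correlation, equal variances and a linear slope, and apply to the four scales; they do not carry over directly to attack counts. Whichever reading is right, ANCOVA has the lower variance at each assumed correlation. It also settles the ambiguity, since its treatment estimate is the same for follow-up and change scores.

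**What to change.** In section 2.14, replace the between-arm t test for PDSS, PASS, HAMA and SCL-90 with ANCOVA of the score on arm and baseline score at each planned time point, including follow-up. A repeated-measures model with baseline as covariate would serve equally. Report the adjusted difference with its 95% confidence interval. An analysis at week 12 alone would not do, because section 2.10.1 counts weeks 4 and 8 and the follow-up month within the primary outcome.

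Adjust attack frequency for its baseline value too, for example by negative binomial regression on arm and log(baseline count + 1), with an offset for the counting window, reporting a rate ratio. The window has to be stated for this. Keep the rank-sum test as a sensitivity analysis. Adjustment for recruiting hospital is optional.

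The cost is a change of wording, slightly more analysis work, about one degree of freedom, and ordinary model assumptions that should be checked. No new visits, measurements or patients are needed. The change should be made before unblinding.

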**Methods::**

The parallel designed, exploratory randomized controlled trial will include 70 outpatients with perimenopausal PD recruited from two hospitals of Chinese Medicine. These subjects will be randomly allocated to an intervention group (Group Embedding) and a control group (Group Medication) in a 1:1 ratio. The subjects in the intervention group will receive acupoint catgut embedding treatment two weeks a time in the following predefined acupuncture points: Shenshu (BL23), Sanyinjiao (SP6), Guanyuan (RN4), Ganshu (BL18), Zusanli (ST36) and Pishu (BL20). The included women of the control group will take 0.4 mg Alprazolam tablet orally, 1 tablet a time, 3 times a day. There is a study period of 3 months and a follow-up period of 1 month for each group. The primary outcomes will be the following therapeutic indexes: the frequency of panic attack, Panic Disorder Severity Score (PDSS), and Panic-associated Symptoms Score (PASS) during the observation period and follow-up period. The changes in Hamilton Anxiety Scale (HAMA) Score and Symptom Checklist 90 (SCL-90) Score will also be compared between these two groups. Additionally, functional magnetic resonance imaging (fMRI) and proton magnetic resonance spectroscopy (1H-MRS) scans will be done before and after the observation period to show cranial neuroimaging changes.

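### Two-sample tests are the only between-arm method named for clinical outcomes recorded at weeks 0, 4, 8, 12 and follow-up; a repeated-measures model would use the intermediate scores and protect against response-related loss that differs between arms

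*Protocol article*

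**What the plan says.** Section 2.14 lists the methods by type of data. For measurement data a t "test will be adapted to run comparison among groups", replaced by the Wilcoxon rank-sum test when the data are not normal; before-after change within an arm gets a paired test. The list is meant for all indexes of curative effect. No longitudinal model is named.

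Of the primary outcomes (attack frequency, PDSS, PASS), section 2.10.1 says: "After baseline time, they will be tested at week 0, week 4, week 8 and week 12, and during the follow-up period". Section 2.10.2 gives HAMA and SCL-90 the same visits. fMRI and 1H-MRS are different: section 2.9 schedules them at weeks 0 and 12 only.

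On loss, section 2.13 says "With the consideration of the maximum loss rate of follow up is 20" per cent. Section 2.6 names loss to follow-up and progress that the investigator finds inappropriate among the reasons for withdrawal. Section 2.8 says that participants and treating staff cannot be blinded.

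**The concern.** A two-sample test compares one number per woman. If that number is the week-12 score or the change to week 12, a woman who leaves after week 8 has no value. Her week-4 and week-8 scores are on file but play no part in the comparison.

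What is at stake is bias more than power. Suppose women who are doing badly leave one arm more often than the other. The remaining women in that arm then look better than the arm as randomised, and the difference between arms shifts in that arm's favour. The design leaves room for this. Treatment is open, the side-effect profiles in section 2.12 differ between embedding and alprazolam, and one withdrawal criterion in section 2.6 may depend on response. Imaging outcomes have no intermediate visits, so the point does not reach them.

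**Working it through.** **The plan's own figures.** Section 2.13 gives "Given α = 0.05 bilateral, β = 0.1, power of test 1−β = 0.9" and "the population standard deviation S = 2.12, δ = 2.06".

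- Final t iteration: 2 × [(2.0129 + 1.3002) × 2.12 / 2.06]² = 23.25, so 24 per arm. This reproduces. (The intermediate 23.66 does not: 1.96 and 1.282 give 22.26. It does not change the 24.)
- Allowance for loss: 48 / 0.8 = 60. This reproduces. After a separate rule based on HAMA items, "the sample size is determined at 70", 35 per arm.
- If the full 20% were lost: 35 × 0.8 = 28 per arm. Exact t-test power at SD 2.12 is 0.946. With the SD pooled from the two arm SDs, √[(2.71² + 1.87²)/2] = 2.33, it is 0.902. On these inputs power survives the loss, so bias is the issue.
- Standardised effect: 2.06 / 2.12 = 0.97 SD. It comes from the Kuppermann index, which is not an outcome here, and serves only as a stand-in.

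**Assumptions not in the document.** Correlation between visits is 0.5 to 0.8. Where loss depends on response, a woman's chance of leaving after week 4 or week 8 rises as her recorded score worsens (missing at random). Two estimates of the week-12 difference are compared: the mean difference among women observed at week 12, and a likelihood estimate that also uses the week-4 and week-8 scores of those who left.

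**Results by scenario.**

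| Scenario | Correlation | Observed-at-week-12 comparison | Likelihood estimate |
|---|---|---|---|
| 20% loss in each arm, same dependence on response within each arm, or loss unrelated to response | 0.5–0.7 | bias about 0 | bias about 0 |
| No true effect, one rule in both arms, 35 per arm | – | type I error 0.048 | – |
| One rule in both arms, 20% overall, effect builds up to 0.97 SD | 0.5 / 0.7 | 0.89 / 0.86 SD (−8% / −11%) | 0.97 SD |
| One rule in both arms, 20% overall, full 0.97 SD from week 4 | 0.5 / 0.7 | 0.81 / 0.75 SD (−17% / −22%) | 0.97 SD |
| 30% versus 10% loss, either arm higher | 0.5–0.7 | bias 0.14–0.20 SD, favouring the arm that loses more | bias about 0 |
| No true effect, about 26% versus 9% loss, 35 per arm | – | shift 0.15 SD, type I error 0.093 | – |
| No true effect, 20% in each arm, response-driven in one arm and random in the other | 0.5–0.8 | bias 0.16–0.25 SD, type I error 9–17% | bias within 0.01 SD, type I error 4–5% |

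In the third and fourth rows one rule yields unequal loss because the arm that does worse loses more women: about 26% versus 14% when the effect builds up, and 31% versus 9% when it is full from week 4.

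**How extreme is the last row?** Removing exactly the worst 20% at week 8 from one arm raises that arm's week-8 mean by φ(z₀.₂₀) / 0.8 = 0.35 SD. The week-12 bias then cannot exceed 0.35 × correlation, which is 0.175 SD at 0.5 and 0.280 SD at 0.8. The simulated 0.157 and 0.249 SD are 90% and 89% of those ceilings; the intermediate correlations give 86 to 90%. This row is a near-worst case. With a noisier link between score and leaving, the same design gives 0.13 to 0.19 SD and type I error of 7 to 12%.

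**The case against.** The strongest reply is that the article does not say that the analysis is limited to women with complete data. It states no analysis set, no missing-data rule and no visit for the between-arm test. A condensed article may leave these to a full protocol or analysis plan that is not shown, and a t test could follow imputation in all randomised women. This stands. A reader might infer that the week-12 result rests on completers only, but the text does not support that as a fact, and the missing rule is no finding in itself. What remains is the named method: by itself it uses only observed values, and it draws on earlier visits only if something is added to it. Not every addition would do. Carrying the last score forward turned a true 0.50 SD into 0.45 SD at correlation 0.7, even with equal loss unrelated to response.

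Other parts of the reply also stand:

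- Loss of poor responders does not by itself bias the difference between arms. It must differ between arms, through rate, mechanism or a treatment effect acting on a common rule.
- The 20% is a maximum used for planning, not a forecast.
- Nothing in the document supports response-driven loss in one arm and random loss in the other; section 2.6 applies the same criteria to both.
- The likelihood model does well here because the simulated loss depends only on recorded scores.
- The trial is labelled exploratory, which lowers the stakes but does not make the weaker analysis preferable.

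**Conclusion.** The point holds as a matter of analysis choice. Section 2.14 fixes a two-sample test for outcomes recorded repeatedly, and a better method is available from data that the trial already collects.

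A reader might go further and conclude that the planned comparison is biased, or that its false-positive rate is 9 to 17%. The document does not support that. Bias is possible and can go either way. Its plausible size runs from about 0, through 8 to 22% of a 0.97 SD effect or 0.14 to 0.20 SD, to about 0.25 SD with type I error up to about 17% in the near-worst case. All of these sizes rest on assumed correlations and dropout rules, and the 8 to 22% also on the Kuppermann effect as a stand-in. The point covers attack frequency, PDSS, PASS, HAMA and SCL-90, and not fMRI or 1H-MRS. It is an improvement that should be made, and the plan is not invalid without it. Confidence is medium, because a fuller plan may already handle missing visits.

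**What to change.** In section 2.14, or in the analysis plan if one exists:

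- Make the main between-arm analysis of PDSS, PASS, HAMA and SCL-90 a mixed model for repeated measures in all randomised women with at least one post-baseline score. Include arm, visit, arm by visit and baseline score, with an unstructured covariance.
- Name the arm difference at week 12, with its 95% confidence interval, as the main contrast.
- Analyse attack frequency with a corresponding log-link count model of the same structure, fitted by likelihood so that it rests on the same missing-data assumption.
- Keep the t or rank-sum test as a sensitivity analysis.

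This needs wording and slightly more analysis work, but no new patients, visits or measurements. The model relies on data missing at random given the recorded scores. That is weaker than what a comparison of observed values needs, but it is still an assumption. Women lost before week 4 have no post-baseline score and are still not covered, so their number should be reported by arm.
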